## Methods: monitoring

5

### Data monitoring

5.1

The Centre for Evidence-Based Chinese Medicine at the Beijing University of Chinese Medicine will commit to the data monitoring—including recruitment supervision, allocation administration, integrity checks of the case report forms, and the overseeing of the unblinding. Interim analysis is not applicable for this pilot study.

### Safety monitoring

5.2

At each visit, physicians will document any adverse events. When severe adverse events occur or the patient suffers from progressive OHE and needs intensive medical care, the event will be reported to the ethics committee and data management committee to determine whether an emergency unblinding is necessary for the patient. The data management committee is also authorized to perform the unblinding, access the final data set, and evaluate the outcomes.

## Research ethics and dissemination

6

### Ethics approval

6.1

The ethics committee of Dongzhimen Hospital, affiliated to Beijing University of Chinese Medicine, approved this protocol on August 8, 2017 (DZMEC-KY-2017-23).

### Protocol amendments

6.2

The principal investigator is responsible for presenting protocol modifications to the ethics committee and data management committee before the modifications are implemented. The ethics committee and data management committee should agree upon significant changes to the protocol—including changes to the objectives, sample size, interventions, and study procedures—before their implementation. We will formally document minor changes—such as corrections of typos and clarifications—in the memorandum.

### Confidentiality

6.3

We will write the names of all the participants in abbreviated Pinyin on the case report forms. The participants’ identities, personal information, and medical records obtained from the study are confidential and can only be accessed by the data management committee and ethics committee when necessary. Examined laboratory specimens will be destroyed following clinical regulations (30 days after collection). Informed consent forms, which contain the patients’ signatures, will be stored separately in the archive center.

### Policies of data sharing and distributions

6.4

During the trial, only the data management committee will be authorized to access the full data set (including the grouping information). The principal investigator is allowed to view all intrastudy medical records but not the allocation data. The ethics committee can acquire the patients’ information only if a severe adverse event occurs and premature unblinding is necessary.

The patients’ ID numbers and medical records will be available from the study leader upon reasonable request after the study is complete. Each patient will obtain a copy of his/her case report form after the unblinding.

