### Trial design

1.3

We designed this trial as a double-blinded, randomized, and controlled exploratory trial. We will implement simple randomization with a 1:1 allocation ratio in 72 eligible patients. The primary endpoint is the occurrence of OHE within 24 weeks.

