### Allocation concealment

3.1

The ethics committee will generate a random number table (containing the patients’ IDs) using Microsoft Excel to settle the grouping plan; each group will be assigned 36 IDs, which will be in a disorganized sequence. Each eligible patient will be given a sealed envelope with an ID after enrollment.

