### Blinding

3.2

The interviewers and patients will both be blinded to the grouping information of each participant. The trial drugs and placebos are consistent in color and taste. The ethics committee and data management committee will keep the allocation sequence and grouping information, which they will not release until final analysis or emergency unblinding.

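### The data management committee may see outcomes linked to treatment group during the trial, and the plan does not separate this from its roles in evaluating outcomes and agreeing amendments

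*Protocol article*

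**What the plan says.** All references are to the protocol article.

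- **Blinding.** Section 1.3 calls the trial double-blinded. Section 3.2 says who is meant: "The interviewers and patients will both be blinded to the grouping information of each participant".
- **Custody of the codes.** Under section 3.1, "The ethics committee will generate a random number table". Section 3.2 adds a second keeper: "The ethics committee and data management committee will keep the allocation sequence and grouping information". Both bodies are to hold the codes back up to the final analysis, unless an emergency calls for earlier disclosure. Section 5.1 gives allocation administration and oversight of unblinding to the university's evidence-based medicine centre.
- **Access during the trial.** Section 6.4: "During the trial, only the data management committee will be authorized to access the full data set (including the grouping information". It denies allocation data to the principal investigator, and it limits the ethics committee's access to patient information to severe adverse events that need early unblinding.
- **Outcome role.** Section 5.2: "The data management committee is also authorized to perform the unblinding, access the final data set, and evaluate the outcomes".
- **Amendments.** Section 6.2 requires the ethics committee and the data management committee to agree to significant changes, naming objectives, sample size, interventions and study procedures.
- **Interim looks.** Section 5.1 says that interim analysis does not apply.

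**The concern.** Keeping a sealed allocation list is a custodial task and does no harm. Being permitted to use the full data set with the group variable attached, while patients are still being followed, is different: whoever has that access can tabulate OHE by arm at any time. The plan gives this permission to a committee that also has a say in evaluating the outcomes and in changing the design.

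Three kinds of decision could be affected: how doubtful OHE cases are finally counted, if the committee's outcome role reaches that far; how the results are evaluated; and whether a proposed change to objectives, sample size or procedures is accepted. The primary outcome is a diagnosis of OHE. Section 2.4.3.1 refers that diagnosis to a practice guideline, and I assume that it leaves some room for clinical judgement. For such an endpoint, blinding everyone who can influence the count or the rules is the main protection. Once by-arm access has occurred, it cannot be undone at the analysis stage.

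**Working it through.** **1. Roles side by side.** The plan gives no figure to reproduce here. The check is whether any section separates the committee's roles.

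| Question | Section | Answer in the article |
|---|---|---|
| May the committee see outcomes with group during the trial? | 6.4 | Yes, stated outright |
| Does it have an outcome role? | 5.2 | Yes; timing and blind status not given |
| Does it have a say in design changes? | 6.2 | Yes, jointly with the ethics committee |
| Is there a planned by-arm review that needs this access? | 5.1 | No; no interim analysis, and data monitoring lies with the centre |
| Does emergency unblinding need it? | 3.2, 5.2 | No; one patient's code is enough |
| Does any section keep the roles apart or delay linkage to lock? | 3.1 to 6.4 | No |

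The access rule is stated affirmatively. The fault therefore lies in what the article says, and is not a detail left to a fuller protocol or a statistical analysis plan.

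**2. Custody.** Four sections share out the allocation information: the ethics committee generates it (3.1), the ethics committee and the data management committee keep it (3.2), the centre administers allocation and oversees unblinding (5.1), and the data management committee performs the unblinding (5.2). These statements can be read together, but no single body is named as the one that holds and breaks the codes.

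**3. Sensitivity of the primary test to one event.** Inputs: 36 per arm (section 2.7) and a chi-square test on OHE occurrence (section 4.3). Section 2.7 says that the OHE incidence is not adequately known, so the event counts below are an assumption chosen for illustration.

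With a and b events in two arms of 36, the Pearson statistic on 1 degree of freedom is

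X² = 72 × [a(36 − b) − b(36 − a)]² / [36 × 36 × (a + b) × (72 − a − b)].

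- 2 versus 8: 72 × (56 − 272)² / (36 × 36 × 10 × 62) = 3,359,232 / 803,520 = 4.18, p = 0.041.
- 2 versus 7: 72 × (58 − 238)² / (36 × 36 × 9 × 63) = 2,332,800 / 734,832 = 3.17, p = 0.075.

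With the continuity correction, 36 (half of 72) is subtracted from the absolute difference before squaring:

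- 2 versus 8: 72 × (216 − 36)² / 803,520 = 2.90, p = 0.088.
- 2 versus 9: 72 × (252 − 36)² / (36 × 36 × 11 × 61) = 3,359,232 / 869,616 = 3.86, p = 0.049.

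The tipping point moves by one event with the version of the test. In both versions a single event separates a result below 0.05 from one above it.

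**The case against.** A reader might infer more than the article supports. Three stronger readings fail.

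- **That the access contradicts the stated double blinding.** It does not. Section 3.2 confines the blinding to interviewers and patients and in the same paragraph names this committee as a keeper of the codes. Section 6.4 also keeps allocation from the principal investigator.
- **That the committee cleans data, raises queries or classifies individual OHE cases knowing the arm.** No section says so. Trained postgraduate students complete the case report forms and enter the data (2.3), the centre checks the forms (5.1), and blinded interviewers see the patients. In section 5.2 the outcome role comes last, after unblinding and access to the final data set, so evaluation of results at the end of the trial is a natural reading.
- **That section 6.4 contradicts sections 3.1 and 3.2 on who has the codes.** The word *only* in 6.4 governs the linked data set. The ethics committee can hold an allocation list without holding outcomes.

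It can also be said that the committee can consent to an amendment but is not given the task of proposing one: the principal investigator presents changes and the ethics committee must agree as well. The trial calls itself exploratory and a pilot. The event counts above are chosen to lie on either side of 0.05, and such fragility is common to small trials; it is no evidence that anyone would reclassify a case.

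These points limit the finding but do not remove it. Even if outcomes are evaluated only at the end, the evaluators may by then have had by-arm access throughout. Consent to an amendment is still a decision that knowledge of the arms can sway.

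**Conclusion.** The point holds as a failure to separate roles, with moderate severity. The plan permits one committee to see outcomes by arm during the trial, gives it an outcome role of unstated timing and blind status, and requires its agreement to design changes, while naming no task that needs by-arm data before the end. This weakens the protection of the primary outcome. It does not break the blinding of patients and interviewers, and no stated figure or analysis is wrong.

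The size of any bias cannot be derived from the document. The calculation shows only that the margin is narrow: at 36 per arm one event can move the primary test across 0.05. The conclusion assumes that OHE diagnosis involves some clinical judgement and that the permission in section 6.4 could be used as written. If the committee in practice holds data and codes apart until lock, only the wording needs correction.

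**What to change.** 1. **Section 6.4:** replace the committee's during-trial access to grouping information with access to data without group codes until OHE classification, analysis sets and the database are locked.
2. **Section 5.2:** state what evaluating the outcomes means, who classifies OHE, and that any evaluation before lock is blind to group.
3. **Section 6.2:** state that amendments are decided without sight of outcomes by arm.
4. **Custody:** name one holder of the allocation list who does not see linked outcome data, with single-patient codes released for emergency unblinding. The ethics committee is one candidate, since it already generates the list under section 3.1. As it also receives reports of severe events (5.2) and agrees amendments (6.2), the list should sit with a custodian there who takes no part in those decisions. The evidence-based medicine centre fits less well, because section 5.1 gives it case report form checks and recruitment supervision.
5. **Alignment:** make sections 3.1, 3.2, 5.1, 5.2 and 6.4 agree on who holds the codes and who breaks them.

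The cost is protocol wording and custody of one file, with emergency code requests routed through the list holder. Sample size, visits and analysis do not change. If by-arm access has already been used, the article reporting the trial should say when and by which role.

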## Discussion

7

Research on the treatment of MHE through traditional Chinese medicine is insufficient. With the features of treatment being based on symptom differentiation, traditional Chinese medicine therapy can act as an early intervention in diseases with insidious manifestations (or subclinical diseases) such as MHE, but the evidence does not sufficiently address the lack of consistent diagnostic criteria and has the confirmation of a randomized placebo-controlled trial. We believe this pilot trial might provide a promising approach to treating CHB-induced MHE in antiviral aspects and preventing OHE.
